## Abstract

**Background:**

The study objective is to assess the effectiveness and economic impact of a structured programme to support patient involvement in centre-based haemodialysis and to understand what works for whom in what circumstances and why. It implements a program of Shared Haemodialysis Care (SHC) that aims to improve experience and outcomes for those who are treated with centre-based haemodialysis, and give more patients the confidence to dialyse independently both at centres and at home.

**Methods/Design:**

The 24 month mixed methods cohort evaluation of 600 prevalent centre based HD patients is nested within a 30 month quality improvement program that aims to scale up SHC at 12 dialysis centres across England. SHC describes an intervention where patients who receive centre-based haemodialysis are given the opportunity to learn, engage with and undertake tasks associated with their treatment.

Following a 6-month set up period, a phased implementation programme is initiated across 12 dialysis units using a randomised stepped wedge design with 6 centres participating in each of 2 steps, each lasting 6 months. The intervention utilises quality improvement methodologies involving rapid tests of change to determine the most appropriate mechanisms for implementation in the context of a learning collaborative. Running parallel with the stepped wedge intervention is a mixed methods cohort evaluation that employs patient questionnaires and interviews, and will link with routinely collected data at the end of the study period. The primary outcome measure is the number of patients performing at least 5 dialysis-related tasks collected using 3 monthly questionnaires. Secondary outcomes measures include: the number of people choosing to perform home haemodialysis or dialyse independently in-centre by the end of the study period; end-user recommendation; home dialysis establishment delay; staff impact and confidence; hospitalisation; infection and health economics.

**Discussion:**

The results from this study will provide evidence of impact of SHC, barriers to patient and centre level adoption and inform development of future interventions to support its implementation.

**Trial registration:**

ISRCTN Number: 93999549, (retrospectively registered 1^st^ May 2017); NIHR Research Portfolio: 31566

## Background

In the UK approximately 23,000 people attend in-centre facilities three times a week to receive haemodialysis (HD) [1]. Structural arrangements in dialysis units tend to create an environment in which patients become passive recipients of their care, engaging little with their own treatment. There is considerable evidence of the benefits of supported self-care in long term conditions [2, 3]. Low health literacy amongst dialysis patients is associated with worse survival [4] whereas self-motivation and patient education results in preferable clinical parameters e.g. phosphate control [5] and fluid balance [6]. Dialysis services are experiencing considerable pressure to deliver high quality care in the face of fiscal challenge, often when approaching capacity. An important mechanism to ensure that quality of care is maintained is to engage service users as true partners in their own care; self-management is an ambition in “Kidney Health: Delivering Excellence” [7]. The tradition of self-care extends to the 1,113 UK patients who performed haemodialysis at home in 2014 [1]. In addition to the better survival [8] and quality of life [9] associated with home HD (HHD), increasing HHD from 4.1% in the UK to the 12.9% used in Australia and New Zealand [10] would lead to estimated annual savings to the UK National Health Service of £16M (an increase of 1400 people treated with HHD at a saving of £12000 per patient per year [11]).

SHC describes an intervention where people treated with in-centre HD are given the opportunity to learn tasks relating to their own dialysis treatment. HD treatment is standardised requiring a number of key steps for its preparation, delivery and discontinuation. For SHC to be adopted consistently across dialysis services several changes become necessary. Health care professionals require a change in their roles from one in which they undertake repetitive tasks for patients to one where they become educators and facilitators in order to support patients to take a greater role in their own care. Patients require encouragement to change their expectation of care to one where they become involved in their own treatment. This approach gives centre based dialysis patients access to the benefits of participating in their own care while increasing opportunities for home dialysis.

## Methods/Design

### Aim

This study aims to assess the effectiveness and economic impact of a structured programme to encourage patient involvement in centre-based haemodialysis (HD), and to understand what works for whom in what circumstances and why. This supported self-care intervention is intended to improve experience and outcomes for those who are treated with centre-based haemodialysis, and give more patients the confidence to dialyse independently both at centres and at home.

### Study design and timeline

End points will be quantified following a stepped-wedge introduction of the intervention, in which 6 centres are randomly allocated to start implementation in step 1, with the remaining 6 starting in step 2. Each step lasts 6 months, and including the baseline phase the study lasts 24 months. The study phases are outlined in Fig. 1 and the schedule of instruments in Table 1. The programme entered the baseline phase in October 2016.

**Fig. 1 Fig1:**
[figure not shown]
Stepped wedge evaluation of quality improvement to facilitate shared haemodialysis care

**Table 1 Tab1:** Data collection instruments

Instrument	Frequency	Content
Demography form	Once, at start	Ethnicity, educational level, home and employment circumstances (adapted from [27])
Tasks questionnaire	3 monthly	15 dialysis related tasks (Table 2)
Think Kidneys questionnaire	6 monthly	POS-S Renal symptom score [16], quality of life (EQ-5D-5L [15]), patient activation measure [14]
SHAREHD uptake indicators form	6 monthly	Meta-cognition (memory & concentration [28]), Health literacy [29], dialysis access and attitudes to self-needling
Health economic form	6 monthly	Transport, dependants, arrangements made and duration of attendance for patient and companions who also attend dialysis
Status change form	Event Driven	Transplantation, mortality, changes in dialysis modality & location

### Study setting and participants

The objective is to recruit 600 prevalent in-centre HD patients from the 12 participating renal centres during the baseline phase. All suitable prevalent dialysis patients at selected centres are entered into a screening log and from this patients are approached and given the opportunity to participate in the research with the intention of recruiting up to 50 patients at each site. Once eligible patients have been given study information, informed consent is taken by trained delegated members of the local research team at a subsequent dialysis session. This includes consent for data linkage to hospital episode and UK Renal Registry data. Participants are also given the opportunity to be involved in interviews and workshops conducted by the evaluation team. As the study is questionnaire based we anticipate that more than 90% of approached patients will agree to be recruited to the study.

### Inclusion/exclusion criteria

Inclusion criteria are for patients to be established on centre based HD and have capacity to give written informed consent. Exclusion criteria are those who are too unwell to engage in the study as judged by the clinical team or unable to understand written and verbal communication in English.

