### Outcome measures and quantitative data collection

Efficacy Endpoints - The primary binary outcome is a change in the proportion of sampled HD patients completing 5 or more out of 14 tasks (Table 2). The secondary binary outcome is an absolute increase HHD and in centre independent dialysis of 4% within participating centres.

Quality and Safety Endpoints - Changes in patient activation [14]; quality of life (EQ-5D-5L) [15]; POS-S Renal symptom score [16] will be assessed using the “Your Health Survey” developed as part of the NHS England supported Transforming Participation in Chronic Kidney Disease program [17]. Responses to this survey will be transferred to the UK Renal Registry and uploaded to PatientView [18] for participating patients to review themselves and to be used to inform clinical consultations. Hospitalisation (all-cause and cause specific) will inform cost, benefits and harms assessments. The economic evaluation will take an NHS and social care perspective and will compare SHC with usual care in a cost-utility analysis based on a cost-per quality adjusted life years (QALYs) approach. The EQ-5D-5L will be used to measure health related quality of life at baseline, six and 12 months. Resource use will be estimated from a range of sources including an adapted cost questionnaire [19] and non-participant observation to quantify time spent performing HD tasks by patients and staff.

Hospital Episode Summary data will be used for information on comorbidity at the time of recruitment (by reviewing diagnosis codes from admissions up to 5 years prior to the start of the SHAREHD programme), hospitalisation (all cause and cause specific) before and after the implementation of SHAREHD to assess for benefits and harms, and inform health economic analyses. Similar datasets and diagnostic codes have been used to identify harms from hospital and home-based haemodialysis therapies and assess cost [20].

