### Sample size calculation

Assuming that the baseline level of completing 5 tasks is around 15%, an ICC of 0.05 and an average cluster size of 25 HD patients; then using the STATA stepped wedge command [21] with a stepped wedge design of 3 steps (including baseline) and 12 clusters, with 6 clusters randomised at each step, we will have 90% power to detect an increase in the event rate from 15% to 30% as statistically significant at the 5% two-sided level. If we assume that the baseline level of the secondary outcome measure of HHD is around 2% in participating clusters an ICC of 0.05 and an average cluster size of 25 HD patients; then with a stepped wedge design of 3 steps (including baseline) and 12 clusters, with 6 clusters randomised at each step will we have 80% power to detect an increase in the event rate from 2% to 7.2% as statistically significant at the 5% two-sided level. In recognition of a mortality rate of 17% per annum [20], a background renal transplantation rate and to mitigate the risk of incomplete data collection, the target recruitment per participating site was increased to 50.

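### The 80% power for home haemodialysis rests on a 2% baseline that an in-centre-only cohort cannot have, and its outcome, difference and time point do not match the stated secondary endpoint

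*Protocol article*

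**What the plan says.** All places are in the Protocol article.

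- **Who is in the cohort.** Inclusion/exclusion criteria: "Inclusion criteria are for patients to be established on centre based HD". Study setting and participants: "The objective is to recruit 600 prevalent in-centre HD patients from the 12 participating renal centres during the baseline phase".
- **Power.** Sample size calculation: "If we assume that the baseline level of the secondary outcome measure of HHD is around 2% in participating clusters". With an ICC of 0.05, 25 patients per cluster, 12 clusters and three periods, it claims "80% power to detect an increase in the event rate from 2% to 7.2" per cent, "as statistically significant at the 5% two-sided level". The site target is then raised to 50 to allow for mortality, transplantation and incomplete data.
- **Endpoint.** Outcome measures and quantitative data collection: "an absolute increase HHD and in centre independent dialysis of 4% within participating centres". Abstract, Methods/Design: "the number of people choosing to perform home haemodialysis or dialyse independently in-centre by the end of the study period".
- **Exposure.** Study design and timeline: six centres start in step 1 and the other six in step 2, so all 12 have started from step 2 on.
- **Analysis.** Statistical analysis plan section: primary and secondary outcomes are compared between intervention and control clusters in a mixed logistic model, with time, phase or step as a covariate and the renal unit as a random effect.
- **Data.** Table 1 lists an event-driven status change form that covers changes of dialysis modality and location.

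**The concern.** Four features of the one secondary outcome that has its own power statement do not agree.

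1. **Baseline.** A cohort recruited only from centre-based patients has no home patients at entry. A 2% baseline would mean 0.02 × 300 = 6 home patients in the powered sample (12 × 25), or 0.02 × 600 = 12 in the recruited one. Eligibility allows none.
2. **Components.** The power is for HHD. The endpoint adds independent in-centre dialysis.
3. **Difference.** The power is for 5.2 points (7.2 − 2). The stated target is 4 points.
4. **Time point and comparison.** A count at the end of the study, or an increase within centres, is a before-and-after quantity. The analysis section plans a between-cluster comparison.

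At stake is whether the 80% describes the outcome that will be analysed, and whether a reader could treat a 4-point rise over time as success without a control.

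**Working it through.** **Inputs (Sample size calculation).** 12 clusters, three periods, six clusters with exposure pattern 0,1,1 and six with 0,0,1; m = 25, taken as patients per cluster-period; ICC 0.05; two-sided 5%. The article names a Stata command but gives no formula, so the variance convention below was chosen because it comes close to both stated powers.

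**Formula.** Hussey-Hughes variance of the intervention effect, with I = 12, T = 3, τ² = ICC × v, σ² = (1 − ICC) × v / m:

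Var = Iσ²(σ² + Tτ²) / [(IU − W)σ² + (U² + ITU − TW − IV)τ²]

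Here U = 6×2 + 6×1 = 18, W = 0² + 6² + 12² = 180 and V = 6×4 + 6×1 = 30. So IU − W = 36 and U² + ITU − TW − IV = 324 + 648 − 540 − 360 = 72. Power = Φ(difference/SE − 1.96).

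**Stated figure, v = p1(1 − p1) at the baseline rate.** For p1 = 2%, v = 0.0196, τ² = 0.00098 and σ² = 0.000745. Then Var = 0.000338 and SE = 0.01839.

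| Case | Difference/SE | Power | Stated |
|---|---|---|---|
| 2% to 7.2% | 0.052/0.01839 = 2.83 | 80.7% | 80% |
| 15% to 30% (primary; SE 0.0469) | 0.15/0.0469 = 3.20 | 89.2% | 90% |

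**The 4-point target, same method.** 2% to 6%: 0.04/0.01839 = 2.175, power Φ(0.215) = 58.5%.

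**The cohort's own baseline.** At p1 = 0, v = 0 and the calculation is undefined. Averaging the variance at the two rates makes it computable:

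| Case, averaged variance | SE | Power |
|---|---|---|
| 2% to 7.2% | 0.0273 | 47.8% |
| 0% to 5.2% | 0.0206 | 71% |
| 0% to 4% | 0.0182 | 59% |

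The last two rows assume that HHD stays at 0% in every control period. They show that the 80% does not carry over to this cohort. They do not show that a 0% baseline as such lowers power, since under one convention 0% to 5.2% has more power than 2% to 7.2%.

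**Effect of 50 per site.** With m = 50 and baseline variance, σ² = 0.000372, Var = 0.000176 and SE = 0.01328. For 2% to 6%, 0.04/0.01328 = 3.01 and power is 85%. That needs all 50 to be retained, whereas the increase is there to absorb losses.

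**Background uptake with no intervention effect.** The article gives no background rate, so r per six-month step is an assumption. The cohort starts at 0% and reaches r in step 1 and 1 − (1 − r)² in step 2.

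| r per step | End minus baseline | Exposed minus unexposed, no time term | With categorical step |
|---|---|---|---|
| 1% | 2.0 points | 1.3 | 0 |
| 2% | 4.0 points | 2.6 | 0 |
| 3% | 5.9 points | 3.9 | 0 |

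The last column is a linear check on cluster-period proportions. It is zero because, with a common background rate, the six started and six not-yet-started centres in step 1 have the same proportion.

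**The case against.** The strongest reply has three parts.

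**The planned analysis is controlled.** A reader might infer from the endpoint wording, and from the absence of any control centre at the end, that background uptake will be reported as benefit. The documents do not support that. The analysis section applies a model with time, phase or step to the secondary outcomes, step 1 gives six against six concurrent centres, and a last period without controls is normal in a stepped wedge. With categorical step the spurious effect in the check is nil. This part of the reply stands.

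**The 2% may be centre-wide, and the composite need not start at zero.** The sample size text says "baseline level of the secondary outcome measure of HHD is around 2% in participating clusters", and the endpoint refers to participating centres whereas the primary outcome refers to sampled patients. Some in-centre patients may already dialyse independently. Both observations are fair: the 0% is exact only for HHD in the recruited cohort. But HHD is what the power statement names, and its cluster size of 25, raised to 50 for death and transplantation, is a count of recruited patients. On a centre-wide reading the baseline fits and the cluster size does not.

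**Details belong in a fuller document.** A condensed article may leave event definitions elsewhere. That does not cover figures which the article states and which disagree with each other.

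Nor does it follow that the design cannot serve this outcome. Even with no HHD in the baseline period, the randomised step-1 contrast remains.

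**Conclusion.** The concern holds as a mismatch between stated figures and wording, not as a demonstrated bias.

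- The 80% applies to HHD alone, from 2%, for 5.2 points. HHD in the recruited cohort starts at 0%, and the stated endpoint is a composite with a 4-point target.
- By the method that comes close to both published powers, 2% to 6% has about 58% power at 25 per cluster. This assumes that the 25 is per cluster-period and that the baseline-rate variance was used. With averaged variance even the stated case falls to about 48%.
- An end-of-study count or within-centre 4-point rise has no concurrent control. An assumed background uptake of about 2% per six-month step would reach roughly 4 points by itself. This matters only if that wording is used as the success criterion in place of the step-adjusted model.

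The article does not settle whether the denominator is the cohort or the whole centre. Each reading conflicts with one of its own statements.

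**What to change.** State one denominator and carry it through the abstract, the endpoint section, the sample size and the analysis.

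- **If the cohort is meant:** define the outcome as a move to home HD or independent in-centre dialysis among patients not already independent, classified by step from the status change form. Confirm that the form also captures becoming independent in-centre, because Table 1 lists only modality and location. Analyse with the planned mixed model, specifying step as a categorical effect. A discrete-time hazard model is an option, not a requirement.
- **If a centre-wide rate is meant:** keep the 2% baseline, and use centre denominators in each period for both the analysis and the power.
- **In either case:** report the end-of-study count and the 4% target as descriptive only, and restate the power for the chosen components, baseline and difference.

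For the cohort option the change is mainly to wording and analysis, subject to the check on the form. A centre-wide rate needs per-period centre counts, which Table 1 does not list. The price is a less favourable stated power and a less precise estimate than a before-and-after count would give.

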### Intervention

The intervention at the centre of this study is that centre based HD patients are given the choice to undertake treatment related tasks, listed in Table 2. These range from performing observations, preparatory hygiene, setting up the dialysis machine, securing dialysis access, programming the machine, initiating monitoring and discontinuing/completing dialysis.

**Table 2 Tab2:** Shared Haemodialysis Care treatment tasks (note some tasks are mutually exclusive)

Patient preparation	Machine Preparation & Dialysis Initiation	During and after dialysis
Measuring your weight	Lining your dialysis machine	Responding to your machine alarms
Measuring your blood pressure and pulse	Priming your dialysis machine	Disconnecting the lines and completing your dialysis
Measuring your temperature	Preparing your dressing pack	Applying pressure to your needle sites OR Locking your own tunnelled line
Washing your hands prior	Programming your dialysis machine	Giving your own anaemia injections (such as epoetin)
	Needling your fistula/graft OR Preparing your tunnelled line	
	Connecting the lines to your fistula/graft/tunnelled line and commencing dialysis	

A series of learning events are planned with teams comprising approximately five individuals from each participating site. These include clinicians, nursing staff, patient partners and additional relevant personnel (e.g. psychologist, service managers as determined by individual sites). The learning events are designed to review the objectives of SHC, share patient and clinician experience, teach and review quality improvement methodologies, and develop rapid tests of change to optimise local implementation. Learning is underpinned through the SHC website [12], teleconferences, social media platforms and newsletters, while staff education is supported by a bespoke nursing training course developed during pilot work [13]. A patient advisory group has been established in order to support their involvement and ensure that the programme maintains patient focussed objectives.

### Outcome measures and quantitative data collection

Efficacy Endpoints - The primary binary outcome is a change in the proportion of sampled HD patients completing 5 or more out of 14 tasks (Table 2). The secondary binary outcome is an absolute increase HHD and in centre independent dialysis of 4% within participating centres.

Quality and Safety Endpoints - Changes in patient activation [14]; quality of life (EQ-5D-5L) [15]; POS-S Renal symptom score [16] will be assessed using the “Your Health Survey” developed as part of the NHS England supported Transforming Participation in Chronic Kidney Disease program [17]. Responses to this survey will be transferred to the UK Renal Registry and uploaded to PatientView [18] for participating patients to review themselves and to be used to inform clinical consultations. Hospitalisation (all-cause and cause specific) will inform cost, benefits and harms assessments. The economic evaluation will take an NHS and social care perspective and will compare SHC with usual care in a cost-utility analysis based on a cost-per quality adjusted life years (QALYs) approach. The EQ-5D-5L will be used to measure health related quality of life at baseline, six and 12 months. Resource use will be estimated from a range of sources including an adapted cost questionnaire [19] and non-participant observation to quantify time spent performing HD tasks by patients and staff.

Hospital Episode Summary data will be used for information on comorbidity at the time of recruitment (by reviewing diagnosis codes from admissions up to 5 years prior to the start of the SHAREHD programme), hospitalisation (all cause and cause specific) before and after the implementation of SHAREHD to assess for benefits and harms, and inform health economic analyses. Similar datasets and diagnostic codes have been used to identify harms from hospital and home-based haemodialysis therapies and assess cost [20].

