### Statistical analysis plan

The primary and secondary outcomes will be compared across the intervention and control clusters using a longitudinal random (or multi-level mixed) effects logistic regression model (with time, phase or step), group (intervention or control) and individual patient characteristics such as age and gender as covariates; and the renal unit or cluster as a random effect. These models will take into account the clustering of outcomes by units. The odds ratio estimate for the intervention effect and its associated confidence interval will be reported from the model. Statistical associations between patient characteristics, dialysis schedules and outcomes will also be explored.

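### The stated 80% power for the secondary outcome is for a 5.2-point rise in HHD alone, not the 4-point rise in HHD plus independent in-centre dialysis that defines the endpoint

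*Protocol article*

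**What the plan says.** Four places in the protocol article bear on this point.

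- **Abstract, Methods/Design.** Among the secondary outcomes is "the number of people choosing to perform home haemodialysis or dialyse independently in-centre by the end of the study period". This is a composite of two modes of dialysis.
- **Outcome measures and quantitative data collection.** The secondary binary outcome is given as "an absolute increase HHD and in centre independent dialysis of 4% within participating centres". It is again a composite, now with a numerical target on the absolute scale.
- **Sample size calculation.** The assumption is that the "baseline level of the secondary outcome measure of HHD is around 2% in participating clusters". With ICC 0.05, 25 patients per cluster, 12 clusters and three periods, the claim is "80% power to detect an increase in the event rate from 2% to 7.2% as statistically significant at the 5% two-sided level". Independent in-centre dialysis and a 4-point effect are not mentioned.
- **Statistical analysis plan.** Primary and secondary outcomes go into a mixed-effects logistic model, and "The odds ratio estimate for the intervention effect and its associated confidence interval will be reported from the model". No absolute measure is named.

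**The concern.** The definition and the power statement differ in two respects.

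- **Outcome:** a composite in one place, HHD alone in the other.
- **Effect:** 4 points in one place, 5.2 in the other. Rounding cannot turn one into the other, and no passage explains the change.

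HHD is one component of the composite. Unless independent in-centre dialysis falls, a 5.2-point rise in HHD means a composite rise of at least 5.2 points. The powered effect is then larger than the target.

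At stake is how the result will be read. A non-significant secondary result could be taken as an 80%-powered failure to reach the target, when no power has been stated for that target. Whether the 4% was reached could also be argued either way, depending on which definition is used. And since the target is absolute, an odds ratio alone does not settle it.

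**Working it through.** **Inputs (Sample size calculation section).** I = 12 clusters; T = 3 periods including baseline; 6 clusters cross over at each step; m = 25; ICC ρ = 0.05; two-sided 5%. The calculation takes m as patients per cluster per period and treats each period as an independent sample. That reading reproduces the stated figures. Spreading 25 patients over all three periods does not (at most 40% for the secondary and 49% for the primary).

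**Formula (Hussey-Hughes).** Let v be the total variance of the binary outcome, τ² = ρv and s² = (1 − ρ)v/m. Then

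Var = I s²(s² + Tτ²) / [(IU − W)s² + (U² + ITU − TW − IV)τ²]

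For this design U = 18, W = 180 and V = 30. The bracketed coefficients are 216 − 180 = 36 and 324 + 648 − 540 − 360 = 72, so

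Var = s²(s² + 3τ²) / (3s² + 6τ²), and power = Φ(difference/SE − 1.96).

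**Step 1: reproduce the stated powers, with v = p0(1 − p0) at the control rate.**

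- Secondary, 2% to 7.2%: v = 0.02 × 0.98 = 0.0196; τ² = 0.00098; s² = 0.95 × 0.0196/25 = 0.0007448. Var = 0.0007448 × 0.0036848/0.0081144 = 0.0003382, so SE = 0.01839. Then 0.052/0.01839 = 2.828 and power is 80.7% (stated 80%).
- Primary, 15% to 30%: v = 0.1275, SE = 0.0469, 0.15/0.0469 = 3.198 and power is 89.2% (stated 90%).

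Both agree, so this is taken as the article's method. Variance at the average of the two rates does not reproduce them (47.2% and 78.1%).

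**Step 2: change only the effect.** 7.2 − 2.0 = 5.2 points against 4. For 2% to 6% the SE is still 0.01839, 0.04/0.01839 = 2.175, and power is 58.5%.

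**Step 3: sensitivity to variance and cluster size, 2% to 6%.**

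| Per cluster-period | Control-rate variance | Average-rate variance |
|---|---|---|
| 25 | 58.5% | 34.2% |
| 50, no loss | 85.4% | 57.6% |
| 50 recruited, 17% yearly mortality only | about 79–82% | about 50–54% |
| Needed for 80% | about 43 | about 87 |

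**Step 4: sensitivity to the baseline.** The 2% is given for HHD, and no baseline for the composite appears. For a 4-point rise at 25 per cluster-period with control-rate variance, the baselines below are assumptions:

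| Assumed baseline | SE | Power |
|---|---|---|
| 1% | 0.0131 | 86% |
| 2% | 0.0184 | 58% |
| 4% | 0.0257 | 34% |
| 5% | 0.0286 | 29% |

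**Step 5: scale.** The odds ratio equivalent to a 4-point rise, ignoring clustering:

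- from 2%: (0.06/0.94)/(0.02/0.98) = 3.1
- from 4%: (0.08/0.92)/(0.04/0.96) = 2.1
- from 10%: (0.14/0.86)/(0.10/0.90) = 1.5

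So an odds ratio does not by itself show whether 4 points was reached.

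**The case against.** The best defence is that the power statement is correct for what it says. The 80% for 2% to 7.2% reproduces, and no 80% is claimed for 4 points. The same 25 per cluster first serves the primary outcome (15% to 30%, 90% power), and the irregular 7.2% looks like the difference detectable at that size. That much stands. A reader might infer that the trial as a whole was sized on the secondary outcome, or that its arithmetic is wrong. Neither is supported. This is a conflict between sections, not a miscalculation.

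Second, recruitment is 50 per centre, which on the article's method gives about 85% for 2% to 6%. This stands only as an upper bound. The Sample size calculation section assigns the surplus to death, transplantation and incomplete data, and the Discussion describes the doubling as mitigation of drop-out. If total losses of 25% to 50% a year are assumed, the same method gives about 59% to 80%.

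Third, it is tempting to say that the endpoint has only about 35% power, or needs nearly 90 patients per cluster-period. Those figures change the variance method as well as the effect. On that variance even the stated 5.2 points has only about 47%, so much of the drop is a separate matter. They also rest on the 2% HHD baseline, so they are not the composite's power.

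Fourth, a reader might infer that nothing but an odds ratio will be reported. The article says that the odds ratio will be reported and does not exclude other measures. It is a condensed account, and a full analysis plan may add a risk difference. This limits the scale point to a recommendation that follows from the absolute criterion. The mismatch in outcome and effect does not depend on it.

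**Conclusion.** The concern holds as an inconsistency: the secondary endpoint is a 4-point rise in a composite, and the 80% power belongs to a 5.2-point rise in one component. On the article's own method, the smaller effect from the same 2% baseline has about 58% power at 25 per cluster-period, and about 34% with average-rate variance. With 50 per centre and no loss these become about 85% and 58%.

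All these figures assume independent samples in each period, while the article describes a consented cohort followed for 24 months. They also borrow an HHD baseline. The composite's power is therefore unknown, and 29% to 86% over assumed baselines of 5% to 1% shows how much depends on that missing input. The documents do not support the statement that the endpoint is unpowered at every plausible sample size: at the recruited 50 it depends on retention, variance method and baseline.

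The primary outcome, its target and its analysis model are untouched by this point. It should be fixed, but it does not threaten the trial's main conclusion.

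**What to change.** 1. Use one definition of the secondary outcome and one target effect in the outcome and sample size sections.
2. State the baseline assumed for that outcome. If the composite is kept, this is a composite baseline, not the 2% for HHD.
3. Restate the power for that outcome, baseline and effect, with the number per cluster-period and the variance assumption. Alternatively, describe the outcome as estimation, with no claim of an 80%-powered test. The 34% and 58% above should not be published as the composite's power.
4. If the absolute 4% criterion stays, report the standardised (marginal) risk difference with its 95% CI from the same logistic model, beside the odds ratio, for this secondary outcome.

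The cost is some rewording, a stated power that is likely to be less favourable, and one post-estimation step. No design change or extra data collection is needed.
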